### Investigational Medicinal Product (IMP)

#### Donepezil Mylan®

The study dose of donepezil (5 mg tablet, MYLAN) will be used according to the recommendations by summary of product characteristics (SPC) and will be identical to the dose approved for treating Alzheimer disease and dementia. According to the SPC of donepezil, the dose of 10 mg/day (2 tablets of 5 mg as a single dose) will be reached after 4 weeks at the dose of 5 mg/day. However, if the patient presents efficacy (decrease of OIPN grade) or adverse effects that appear to be related to the study treatment, the investigator will have the option of continuing treatment at a dose of 5 mg/day, until the end of the study.

To improve adherence to intervention protocols, drug tablet return will be counted by pharmacists and during monitoring.

#### Placebo

The donepezil and the placebo tablets will be in identical opaque blister and will have the same shape, the same colour and the same branding. The placebo will be taken for 16 weeks with the same administration modalities as the donepezil group.

Patients will be given a diary to remind them of their treatment dosage and to indicate any deviations in their intake. Adverse events will be collected by patients throughout the study in their diaries and during the various visits. The type, intensity and potential relationship with the study treatment will be informed.

Treatment should be discontinued if:AST or ALT levels ≥ 3 times normal values,Appearance of severe cardiovascular disease (as determined by clinician), bradycardia (< 55 bpm), cardiac conduction disturbances (assessed by electrocardiogram),Development of peptic ulcer disease,Development of asthma or obstructive lung disease,Development of an allergy to donepezil or piperidine derivatives.Pregnancy

Investigators will be allowed to unblind without sponsor intervention in case of emergency (e.g. serious adverse event, death, pregnancy).

### Study endpoints

#### Primary endpoint—QLQ-CIPN20 questionnaire (sensory scale)

The EORTC was developed the QLQ-CIPN20 questionnaire as an auto-questionnaire specifically to assess CIPN severity. The QLQ-CIPN20 contains 20 questions about the patients’ experience regarding functional limitations and symptoms related to their CIPN. This auto-questionnaire consist of 3 subscales: sensory, motor and autonomic, which permit a comprehensive picture of the characteristics of CIPN. This auto-questionnaire has been previously validated in clinical trials [52, 53]. The literature suggests that the assessment of CIPN symptoms is preferable with Patient-Reported Outcomes (PROs) rather than Clinician-Reported Outcomes (CROs). Moreover, the QLQ-CIPN20 questionnaire is considered as one of the most appropriate outcome measures [54–56].

The sensory subscale assesses various symptoms such as paraesthesia, dysesthesia, numbness and pain; and is more relevant to assess CIPN than the 11-point numerical rating scale (NRS) for pain, which is specific only for pain symptoms which affects only 30% of patients [4, 5]. Other studies have demonstrated that the comparison of QLQ-CIPN20 and the NCI-CTCAE sensory neuropathic grade provides convergent validity [57, 58]. The QLQ-CIPN20 also provided more detailed information, permitting to distinguish more severity degrees of neuropathy, and was more responsive to change over time than the NCI-CTCAE [58]. Finally, as our study will be a multicentre trial, using the QLQ-CIPN20 will make it possible to carefully standardize the assessment of OIPN between centres.

For the primary endpoint (percentage of responders to the treatment), only the sensory scale scores will be used. According to the studies of Alberti et al*.* [57] and Le-Rademacher et al*.* [58], the sensory scale score can be correlated with the NCI-CTCAE sensory neuropathy grade (QLQ-CIPN20 scores < 30: grade 1, ≥ 30 and ≤ 40: grade 2, and > 40 / 100: grade 3–4).

A responder will correspond to a patient moving from a score ≥ 30 and ≤ 40 to a score < 30 / 100 or from a score > 40 to a score ≤ 40 / 100.

Because of the absence of preliminary clinical results in the literature about donepezil and CIPN, and the recommendations of international experts (expertise of our project in the framework of a call for projects), we will perform a proof-of concept study to generate preliminary results for a future randomised placebo-controlled phase 3 study if the results are positive. Then, for the primary endpoint, the responder rate will not be compared to placebo, but assessed only for the donepezil arm after 16 weeks of treatment. Donepezil will be considered effective if 7 or more responders are observed in the 33 patients of the donepezil arm (see “statistics” paragraph for details). The responder rate will be compared to the placebo arm only for the secondary endpoint.

In the event of a beneficial therapeutic effect at the end of treatment (significant reduction in neuropathic disorders [reduction of one grade of neuropathy (according to NCI-CTCAE v4.0 or QLQ-CIPN20 score) or -30% of neuropathic pain (according to NRS 0–10 scale), if present, or PGIC score of 6 or 7]), the investigator will be allowed to request a lifting of the treatment blind, to adapt the further management of the patient and/or refer the patient to a specialist (neurologist, pain physician).

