#### End of study treatment visit (V4)

The visit will take place after 16 weeks of treatment or after study treatment discontinuation. The following will be performed:The patient will return the empty or unused study treatment from the last treatment period,Clinical examination to assess the grade of neuropathy (NCI-CTCAE v4.0),Completion of study questionnaires (QLQ-CIPN20, HADS and QLQ-C30),Neuropathic pain assessment: 11-point NRS, and if pain score ≥ 4 / 10 then perform the DN4 interview and complete the NPSI questionnaire if the DN4 interview is positive (score ≥ 3 / 7),Assessment of painkiller consumption (if applicable),Electrocardiogram and heart rate,Blood sampling (hepatic function, complete blood count),Body weight,Assessment of safety (adverse effects by NCI CTCAE v4.0).

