#### Post study treatment follow-up phone call

This phone call will be planned 1-month after the “End of study treatment visit”.

The following will be performed during the post-treatment phone call:Neuropathic pain assessment: 11-point NRS, and if the pain score ≥ 4 / 10 then the perform DN4 interview and complete the NPSI questionnaire if the DN4 interview positive (score ≥ 3 / 7),Completion of study questionnaires (QLQ-CIPN20),Assessment of painkiller consumption (if applicable),Evaluation of safety (adverse effects by NCI CTCAE v4.0).All the questionnaires will be given to the patients during V4 to allow them to complete the questionnaires at home after 1-month. The phone call will remind the patients to return the completed questionnaires to the investigating centre.

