#### Statistical analysis

All statistical analyses will be performed using SAS software version 9.4 before breaking the randomization codes, according to International Conference on Harmonization-Good Clinical Practice guidelines. A two-sided *p*-value of less than 0.05 will be considered for the statistical significance of all the analyses. The results will be expressed as hazard-ratios and 95% confidence intervals. Secondary analyses will be exploratory.

The baseline description of the patients included in the analysis will be carried out, without presenting inferential statistical tests (according to recommendations). As part of a proof-of-concept, only patients who have completed the study (treatment received in its entirety for 16 weeks whatever the dose = per protocol population) will be analyzed for the primary endpoint. The primary endpoint will be the rate of responders and will be described using frequency and percentage. A 95% one-sided confidence interval will also be calculated. Subgroup analyses for the primary endpoint will be planned for each stratum of the randomization (neuropathy grade, age of neuropathy and type of chemotherapy).

For the secondary endpoints, analyses will be performed on the intention-to-treat and per-protocol populations and compared to the placebo arm.

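### Optional unblinding of improved patients at end of treatment can precede their week-20 self-reports, so blinding may be lost according to outcome

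*Protocol article*

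**What the plan says.** - **The permission.** The Primary endpoint section describes a non-emergency code break. The condition is "In the event of a beneficial therapeutic effect at the end of treatment", and the consequence is that "the investigator will be allowed to request a lifting of the treatment blind, to adapt the further management of the patient". Qualifying benefit includes "reduction of one grade of neuropathy (according to NCI-CTCAE v4.0 or QLQ-CIPN20 score"), a 30% fall in neuropathic pain, or a PGIC of 6 or 7. Emergency unblinding is separate and is dealt with in the Placebo section.
- **The primary endpoint.** The same section defines response by downward crossing of the 30 or 40 cut-off: "A responder will correspond to a patient moving from a score ≥ 30 and ≤ 40 to a score < 30 / 100", or from above 40 to 40 or less. The rate is "assessed only for the donepezil arm after 16 weeks of treatment".
- **End of treatment.** For V4, "The visit will take place after 16 weeks of treatment or after study treatment discontinuation".
- **Follow-up.** The Study design section gives 20 weeks per patient, the last 4 of them follow-up. The follow-up call is one month after V4 and covers pain NRS (with DN4 and NPSI if triggered), QLQ-CIPN20, painkiller use and adverse effects. "All the questionnaires will be given to the patients during V4 to allow them to complete the questionnaires at home after 1-month".
- **Blinding and analysis.** The Study design section calls the trial triple-blinded: patients, clinicians and pharmacists. The Statistical analysis section has all analyses performed "before breaking the randomization codes", and plans arm-by-time mixed models for repeated data.
- **Treatment changes.** The text under Exclusion criteria bars any change of OIPN or pain therapy for the duration of the study. It also allows a patient to be withdrawn from analysis if antineuropathic or analgesic therapy is modified.

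**The concern.** The permission is triggered by the outcome. Only patients judged improved qualify, and they may learn their allocation before their last set of mostly subjective measurements. Someone who learns that the improvement came on placebo may report symptoms differently a month later from someone who learns that it came on donepezil. Assessors are exposed too: the DN4 interview is clinician-administered, and adverse events are classed as related to treatment or not.

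If donepezil works, more of its patients qualify, so the loss of blinding would also differ by arm. What is at stake is the week-20 comparison with placebo and any longitudinal model that includes that time point. The comparison is secondary and exploratory, but the Discussion relies on the placebo arm to strengthen the evidence.

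The permission also sits awkwardly with three other statements: the triple-blind label, the bar on changing OIPN or pain therapy during the study, and the promise about the timing of analysis relative to the code break.

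**Working it through.** **1. Order of events.**

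| Time | What happens | Section |
|---|---|---|
| Week 16 (or discontinuation) | V4: QLQ-CIPN20, CTCAE grade, NRS and other assessments | End of study treatment visit (V4) |
| From V4, no later limit stated | Unblinding may be requested for a patient with benefit | Primary endpoint |
| V4 + 1 month | QLQ-CIPN20 at home; NRS, painkillers, adverse effects | Post study treatment follow-up phone call |

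Nothing shown puts the second row after the third, or says how follow-up data are treated once a code has been opened.

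**2. Trigger against endpoint.** Every primary responder drops at least one QLQ-CIPN20 grade band, so every responder meets the trigger. The other triggers can only add patients. The responder rate is thus a lower limit for the proportion *eligible*. It is not a lower limit for the proportion *unblinded*, because requests are optional.

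**3. The plan's own figures.** Sample size estimation states: reject if at least 7 of 33 respond, p0 = 0.10, p1 = 0.30.
- Type I error: P(X ≥ 7 | n = 33, p = 0.10) = 0.0417, as stated.
- Power: P(X ≥ 7 | n = 33, p = 0.30) = 0.9056, against the stated 91%.

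Both reproduce. Neither depends on the unblinding rule.

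**4. Patients eligible on the QLQ-CIPN20 trigger alone.** Inputs: 33 evaluable per arm (Sample size estimation); 30% on donepezil (the plan's alternative); placebo rate *assumed*, because the article gives none. Expected number = 33 × p(donepezil) + 33 × p(placebo).

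| Donepezil | Placebo (assumed) | Donepezil n | Placebo n | Total of 66 | Share | Ratio of arms |
|---|---|---|---|---|---|---|
| 30% | 10% | 9.9 | 3.3 | 13.2 | 20% | 3.0 |
| 30% | 20% | 9.9 | 6.6 | 16.5 | 25% | 1.5 |
| 30% | 30% | 9.9 | 9.9 | 19.8 | 30% | 1.0 |
| 10% (null) | 10% | 3.3 | 3.3 | 6.6 | 10% | 1.0 |

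**5. Permission against the other statements.**
- *Therapy changes.* The code break exists so that management can be adapted, yet the study runs to week 20 and changes to OIPN or pain therapy are barred until it ends. Read literally, an improved patient whose therapy is changed in weeks 16 to 20 could be withdrawn from analysis.
- *Analysis before code break.* Read literally, this fails once any individual code has been opened. Read as referring to the trial-level list, it can stand, but the text does not say so.

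**The case against.** The strongest reply is that this is a small matter of operational detail. In the permission, the end of treatment dates the benefit, not the code break. The investigator has to request it, whereas emergency unblinding needs no sponsor involvement, which suggests a controlled step. A condensed article may leave its timing to the full protocol, and the exposed data are one off-treatment assessment in analyses declared exploratory. Much of this stands and limits the severity. It does not remove the point: the article expressly grants outcome-triggered unblinding, expressly collects self-reports afterwards, and states no order between them.

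A reader might infer stronger claims that the document does not support:

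- *A threefold imbalance between arms.* This treats the 10% in the sample size section as a placebo rate. It is the null rate for the donepezil arm. The Discussion itself calls the placebo effect very important in pain relief therapies, and at higher placebo rates the ratio falls to 1.5 or 1.
- *A guaranteed share of open-label records.* Eligibility is not unblinding; the actual number may be anything from none upward.
- *A compromised primary endpoint.* The week-16 score is collected at V4 and is itself needed to meet the QLQ-CIPN20 trigger. The remaining gap is that the article does not say all V4 assessments must precede a request.
- *A blinded analysis that is impossible.* Rates and confidence limits can be computed for coded arms, and the rule of 7 applied when the arms are identified. One patient's allocation told to one investigator does not release the list to the analyst.
- *Mixed models that are certainly biased.* The article does not list their time points; including week 20 is plausible but inferred.

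**Conclusion.** The concern holds in limited form. As written, the plan permits outcome-dependent loss of blinding before the week-20 self-reports, and this loss would also depend on arm if the drug works. The exposure is confined to the exploratory week-20 between-arm data and any longitudinal model that uses them. The primary result is largely unaffected provided the V4 questionnaires are finished before any request.

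On the QLQ-CIPN20 trigger alone, about 13 to 20 of 66 evaluable patients (20% to 30%) would be eligible. This assumes the plan's 30% on donepezil and a placebo rate between 10% and 30%, which is an assumption of this review. The other triggers could raise the number eligible, and the optional nature of the request could make the number actually unblinded lower. The direction and size of any resulting bias cannot be derived from the document.

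The conflict with the statement on analysis before code break is one of wording. The conflict with the bar on therapeutic change needs reconciling. This is worth correcting, but it does not threaten the go/no-go decision.

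**What to change.** 1. Reconcile the unblinding permission, the bar on therapeutic change, the follow-up assessments and the statement on code breaking. Which clinical rule should prevail is for the sponsor and investigators.
2. Require all V4 assessments to be recorded before any non-emergency request.
3. Where patient management allows, process such a request only after the week-20 questionnaires and adverse-effect report have been captured. Leave emergency unblinding unchanged.
4. Log every code break with its date, and flag week-20 records collected after one.
5. Report the week-20 between-arm results with a sensitivity analysis for flagged records. Do not simply drop them: they come from improved patients, so exclusion would itself select on outcome.
6. Reword the Statistical analysis section to say that the database is locked and the analysis plan final before the trial-level randomisation list is released.

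The cost is a delay of up to about 4 weeks for a non-urgent code break, some added analysis work, and wording changes. Sample size, type I error and power do not change.

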#### Secondary endpoints

The evolution of all the secondary parameters will be studied in an intragroup (before *vs.* after treatment) and an intergroup (placebo *vs.* donepezil arm): i) Sensory, motor and autonomic scales from the QLQ-CIPN20 questionnaire (see below); ii) Grading of OIPN by NCI-CTCAE v4.0: this scale will be used to grade the severity of sensory neuropathy from 1 to 4 (1 = Asymptomatic, 2 = Moderate symptoms; limiting instrumental of Activities of Daily Living [ADL], 3 = Severe symptoms; limiting self-care ADL, 4 = Life-threatening consequences; urgent intervention indicated); iii) Assessment of neuropathic pain: monthly assessment of pain felt in the last week by 11-point NRS. This scale is used for adults and children 10 years old or older patient self-reporting of pain (score of 0 = no pain and 10 = worst possible pain). If NRS ≥ 4/10, neuropathic pain will be validated by the DN4 interview questionnaire (“*Douleur Neuropathique 4*”) will be mandatory. The interview portion of the DN4 questionnaire is a clinician-administered screening tool for neuropathic pain [59]. The questionnaire includes 7 items (YES or NO, the test is positive for a score ≥ 3/7). If the patient have a positive DN4 and a pain intensity ≥ 4/10 (NRS), neuropathic pain will be confirmed and will be characterized by the Neuropathic Pain Symptom Inventory (NPSI) questionnaire. This self-reported questionnaire assesses neuropathic pain symptoms [60], and includes 12 items; iv) HRQoL by the QLQ-C30 questionnaire (EORTC): this auto-questionnaire (EORTC) assesses the HRQoL of cancer patients, and includes five functional scales, three symptom scales, an overall HRQoL scale, and a number of additional elements assessing other symptoms; v) Anxiety and depression by the hospital anxiety and depression scale (HADS) questionnaire: this auto-questionnaire detects anxiety and depressive disorders, and includes 14 items rated from 0 to 3 (7 questions for anxiety and 7 for depression). The following interpretation is proposed for each of the two total scores: ≤ 7: absence of symptomatology; 8 to 10: suggestive symptomatology; ≥ 11: indicative symptomatology; vi) Patients’ Global Impression of Change (PGIC): PGIC [61] assesses the general effectiveness of the treatment according to the impression of patient, with the scores from 1 to 7 (from aggravated to very improve); vii) Safety: the time to treatment failure will be assess. This is the interval between randomization to treatment discontinuation for any reason. The assessment of adverse events (AEs) associated with study treatment will be also assessed by NCI-CTCAE v4.0. Any AEs will be collected daily by the patient and during the monthly visits. AEs will be categorized according to their intensity, treatment-related or not and by type. At last, viii) Assessment of painkiller consumption (if any): drug consumption for OIPN will be assessed throughout the study.

### Methodology and study design (Fig. 1)

**Fig. 1 Fig1:**
[figure not shown]
Study Design and evaluations

#### Enrolment

Colorectal and pancreatic cancer survivors having received oxaliplatin-based chemotherapy and eliciting peripheral neuropathy of a grade ≥ 2 (QLQ-CIPN20 sensory scores ≥ 30 / 100) will be included by clinicians to receive either placebo or donepezil. Patients will either be contacted by phone to propose the study or during one of their consultations at the clinical centre.

#### Inclusion/randomization visit (V0)

The study will be presented to the patient, along with the objectives, organization, constraints, and assessment questionnaires. If the patient accepts to participate, they will confirm it by signing the informed consent form prior to any study procedure. The following will be performed:Validation of patient eligibility (inclusion and non-inclusion criteria),Clinical examination and body weight,Electrocardiogram and heart rate,Blood sampling (hepatic and renal function, complete blood count),Verification of presence of OPIN (QLQ-CIPN20),Randomization,Completion of study questionnaires (HADS and QLQ-C30),Neuropathic pain assessment: 11-point NRS, and if pain score ≥ 4 / 10 then perform DN4 interview and complete NPSI questionnaire if DN4 interview positive (score ≥ 3 / 7),Assessment of painkiller consumption (if applicable),Delivery of study treatment according to randomization for a 4-week period: donepezil or placebo.

#### Visits after 4, 8 and 12 weeks of initiation treatment (V1, V2 and V3)

The following will be performed:The patient will return the empty or unused study treatment from the last treatment period,Completion of QLQ-CIPN20 questionnaire and 11-point NRS pain,Assessment of painkiller consumption (if applicable),Electrocardiogram and heart rate,Blood sampling (hepatic function, complete blood count),Body weight,Assessment of safety (adverse effects by NCI CTCAE v4.0),Determination of the dose to be delivered according to the treatment efficacy and tolerance, for the 4-weeks period. In the case of efficacy or poor tolerance, the dose will remain at 5 mg/day. If the study treatment is well tolerated but does not show efficacy (according to QLQ-CIPN20 score), the dosage will be increased to 10 mg/day.

#### End of study treatment visit (V4)

The visit will take place after 16 weeks of treatment or after study treatment discontinuation. The following will be performed:The patient will return the empty or unused study treatment from the last treatment period,Clinical examination to assess the grade of neuropathy (NCI-CTCAE v4.0),Completion of study questionnaires (QLQ-CIPN20, HADS and QLQ-C30),Neuropathic pain assessment: 11-point NRS, and if pain score ≥ 4 / 10 then perform the DN4 interview and complete the NPSI questionnaire if the DN4 interview is positive (score ≥ 3 / 7),Assessment of painkiller consumption (if applicable),Electrocardiogram and heart rate,Blood sampling (hepatic function, complete blood count),Body weight,Assessment of safety (adverse effects by NCI CTCAE v4.0).

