Descriptive statistics will be presented by treatment arms. Continuous variables will be presented as mean and standard deviation (otherwise as median and interquartile range) and will be compared between arms using the unpaired t test or the Mann–Whitney U test when appropriate according to the assumptions of the t-test: (i) the Shapiro–Wilk test will be used to assess normality, and (ii) the Fisher-Snedecor test to assess homoscedasticity. When appropriate (for example, for the sensory scores of the QLQ-CIPN20), these analyses will be supplemented by the recommendations proposed by Vickers and Altman, i.e. ANCOVA, considering baseline scores as covariates. Then, multiple linear mixed models could be run with centers as random-effects. Covariates will be determined according to univariate results and to their clinical relevance, including stratification parameters. The normality of residuals will be studied as described previously. If appropriate, a transformation (for example logarithmic) should be proposed to achieve the normality of dependent variable. The results will be expressed as regression coefficients and 95% confidence intervals. The analyses of other continuous secondary endpoints (11-point pain NRS, DN4 interview, NPSI, HADS and QLQ-C30 questionnaires) will be carried out similarly. For categorical parameters (adverse effects, PGIC, DN4 interview or HADS categorized according to literature), Chi-squared or Fischer exact tests will be used to compare the treatment arms. A generalized linear mixed model (more precisely logistic regression for dichotomous outcomes) will be applied for multivariable analyses. The results will be expressed as relative risks and 95% confidence intervals.

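### DN4 and NPSI are collected after treatment only in patients still in pain, which does not fit the planned continuous between-arm analysis of those scores

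*Protocol article*

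**What the plan says.** All references are to the protocol article.

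- **Inclusion/randomization visit (V0):** "if pain score ≥ 4 / 10 then perform DN4 interview and complete NPSI questionnaire if DN4 interview positive".
- **End of study treatment visit (V4):** the same two-step rule, applied to the pain score at V4: "if pain score ≥ 4 / 10 then perform the DN4 interview and complete the NPSI questionnaire if the DN4 interview is positive".
- **Post study treatment follow-up phone call:** the same rule again: "if the pain score ≥ 4 / 10 then the perform DN4 interview and complete the NPSI questionnaire if the DN4 interview positive".
- **Secondary endpoints:** the gate is described as diagnostic. With NRS at least 4/10 and DN4 at least 3/7, "neuropathic pain will be confirmed and will be characterized by the Neuropathic Pain Symptom Inventory (NPSI) questionnaire". The same section says "The evolution of all the secondary parameters will be studied in an intragroup" comparison (before v after) and also between placebo and donepezil.
- **Statistical analysis:** after setting out t test or Mann-Whitney, ANCOVA and mixed models, it says "The analyses of other continuous secondary endpoints (11-point pain NRS, DN4 interview, NPSI, HADS and QLQ-C30 questionnaires) will be carried out similarly". The ANCOVA is specified as "ANCOVA, considering baseline scores as covariates". DN4 also appears among the categorical parameters.

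No section asks for DN4 or NPSI to be repeated in a patient who qualified at V0 but has less pain later. None gives a score to such a patient.

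**The concern.** At V0 the gate is a reasonable screen, because it acts on pain before treatment starts. At V4 the NRS is itself an outcome of treatment. A patient who goes from 7/10 to 2/10 has no V4 DN4 or NPSI and cannot contribute a paired score to an ANCOVA or a before-after comparison. NPSI also needs a positive DN4, which is a second gate that depends on outcome.

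A between-arm comparison of the scores that exist is therefore a comparison among patients still in pain, and a working drug changes who those patients are. Within each arm, the before-after change also leaves out those who improved past the gate.

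Neuropathic pain compared with placebo is a listed secondary objective, and the trial is meant to inform a phase 3 study. An NPSI result that misstates a real effect could mislead that planning.

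**Working it through.** **Plan's own figures.** The article gives no figure for DN4 or NPSI. Its primary-design figures reproduce by exact binomial: P(X ≥ 7 | n = 33, 10%) = 0.0417 and P(X ≥ 7 | n = 33, 30%) = 0.906, stated as 91%. This point does not touch them.

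**Check 1: NRS gate at V4 only, closed form.** Assumed inputs, none from the documents:
- V4 NRS normal, mean 5 and SD 2 on placebo; a donepezil benefit of 1 or 2 NRS points for everyone
- whole-number NRS, so the cut is at 3.5
- NPSI SD 18, and a true NPSI difference of 9 or 18 points (0.5 or 1 SD, matching the NRS shift)
- NRS-NPSI correlation ρ of 0.6, 0.7 or 0.8

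With a = (3.5 − mean)/2, the share scored is 1 − Φ(a). The mean NPSI of those scored is raised by ρ × 18 × λ, where λ = φ(a)/(1 − Φ(a)).

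| V4 mean NRS | share scored | λ |
|---|---|---|
| 5 (placebo) | 77% | 0.389 |
| 4 (1-point benefit) | 60% | 0.646 |
| 3 (2-point benefit) | 40% | 0.964 |

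Observed difference = true difference − ρ × 18 × (λ donepezil − λ placebo):
- 2-point benefit: 18 − ρ × 18 × 0.574 = 11.8, 10.8, 9.7 for ρ = 0.6, 0.7, 0.8 (66%, 60%, 54% retained)
- 1-point benefit: 9 − ρ × 18 × 0.256 = 6.2, 5.8, 5.3 (69%, 64%, 59% retained)

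**Check 2: both gates at both visits, with ANCOVA on baseline.** Simulation with 1,000,000 patients per arm. Assumed: baseline NRS mean 5, SD 2; mean change −0.5, SD 2; NPSI about 8 × NRS plus noise; probability of a positive DN4 rising with NPSI. The true contrast is taken in everyone who qualified at V0; the gated contrast is the ANCOVA in those who also pass at V4. The NRS benefit is the nominal mean, before scores are bounded at 0.

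| Pattern of benefit | NRS benefit | V0-qualified scored at V4, placebo / donepezil | true | gated | retained |
|---|---|---|---|---|---|
| none | 0 | 66% / 66% | 0.0 | 0.0 | – |
| uniform | 1 | 66% / 52% | −7.5 | −4.0 | 53% |
| uniform | 2 | 66% / 38% | −14.7 | −7.6 | 52% |
| 50% responders | 1 | 66% / 52% | −7.4 | −2.8 | 38% |
| 50% responders | 2 | 66% / 40% | −13.5 | −2.6 | 19% |
| 30% responders | 1 | 66% / 52% | −7.1 | −1.4 | 20% |
| 30% responders | 2 | 66% / 47% | −11.0 | −0.3 | 3% |
| only those who would otherwise be below 6/10 | 1 | 66% / 54% | −4.3 | +0.9 | sign reversed |
| only those who would otherwise be below 6/10 | 2 | 66% / 44% | −8.3 | +4.0 | sign reversed |

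**Numbers of patients.** The Background puts neuropathic pain at about 30% of patients with sensory CIPN. On 40 per arm that is 12. Paired NPSI scores would then exist for about 12 × 0.66 = 8 placebo patients, against 12 × 0.52 = 6 or 12 × 0.38 = 5 donepezil patients under uniform benefit.

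**Do the missing-data provisions repair it?** The worst case in the Statistical analysis section counts patients with missing data as not reacting, so a relieved patient would be scored as a failure. Multiple imputation could use the observed NRS. But the gate yields no DN4 below NRS 4, and no NPSI below NRS 4 or with a negative DN4, so the imputed values would be extrapolation.

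**The case against.** Several objections carry weight.

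- **Direction.** A reader might infer that any donepezil effect on DN4 or NPSI is pulled toward zero. The documents give no basis for that certainty, and the simulation contradicts it: when only milder patients benefit, the sign changes. This stands.
- **Size.** All distributions are assumed. Check 1 omits the V0 gate, the DN4 gate and the ANCOVA, so its loss of 31-46% is one scenario and not an estimate. Bias in the DN4 score was not simulated. This stands.
- **Categorised DN4.** The Statistical analysis section also allows a categorical DN4 analysis, and Secondary endpoints defines confirmed neuropathic pain as NRS ≥ 4 with DN4 ≥ 3. A patient below 4/10 could count as not having it and stay in that comparison. The article does not state this rule, but the reading is plausible, so the problem is confined to the continuous scores.
- **Practical weight.** Secondary analyses are declared exploratory. With 10 patients per arm (30% of 33) and SD 18, the standard error of an NPSI difference is 18 × √(2/10) = 8 points with nobody missing, so a 3-4 point distortion is under half a standard error. The 30% figure concerns sensory CIPN in general, whereas this trial enrols grade 2 or higher. This limits the importance but does not remove the defect.
- **Documents not shown.** Scoring of patients below the gate may be left to the SAP, and a complete-case analysis is not stated. But an SAP cannot recover scores that the visit schedule tells sites not to collect. At follow-up, questionnaires are handed out at V4 for home completion, so how the gate acts on the self-completed NPSI there is unclear.

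**Conclusion.** The concern holds for the continuous DN4 and NPSI scores after treatment. Collecting them behind a post-treatment pain gate is incompatible with comparing them between arms, or before and after, as ordinary continuous endpoints. If donepezil works, attenuation is the usual result. Under the assumed distributions with uniform benefit, roughly 50-70% of the NPSI effect survives; with benefit concentrated in responders, 3-38%. The true size cannot be known from the documents, and in some patterns the sign is not assured either.

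With no drug effect the between-arm contrast is unbiased, so the gate does not create a spurious between-arm benefit under the null. A reader might also infer that the trial's main result or its whole pain assessment is compromised. That is not supported: the primary endpoint is the QLQ-CIPN20 sensory score, and both it and the pain NRS are collected without a gate at V4 and follow-up.

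**What to change.** Apply the NRS/DN4 gate only at V0, to define the neuropathic-pain set. Every patient in that set completes DN4 and NPSI at V4 and at follow-up, whatever the NRS is then. The continuous DN4 and NPSI comparisons use this baseline-defined set. Patients who newly reach 4/10 after V0 are described separately.

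For the categorical analysis, a yes/no endpoint of confirmed neuropathic pain (NRS ≥ 4 and DN4 ≥ 3) may be used, with NRS below 4 counted as no. It can be classified for every patient assessed.

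The V4, follow-up, Secondary endpoints and Statistical analysis sections need matching wording, including how the follow-up NPSI is triggered.

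The cost is a 12-item self-questionnaire and a 7-item interview at contacts already planned, for about 20-25 patients (30% of 66 is 20; 30% of 80 is 24). Sample size, visits and treatment do not change.
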